## Abstract

**Background:**

InCharge is a newly developed school-based health intervention aimed at older adolescents. It aims to promote a healthier lifestyle by increasing self-regulation skills. After the InCharge program’s effectiveness was previously investigated in a pilot study, the content of the program was adapted.

**Objective:**

This study describes the protocol of a cluster randomized controlled trial that aims to investigate the effectiveness of the InCharge program.

**Methods:**

A cluster randomized controlled trial including 70 classes with older adolescents (aged 16 years or older) in the Netherlands will be conducted to test the effectiveness of the InCharge program. After schools are recruited, randomization occurs at the class level. The trial consists of the following two conditions: an experimental condition and a control condition. Participants in the experimental condition will be given the InCharge intervention, consisting of four lessons of 50 minutes, with each lesson containing three assignments of approximately 15 minutes. While participants in the experimental condition will receive InCharge, participants in the control condition will receive regular academic school courses. Surveys are administered 1 week before the intervention (baseline), 1 week after the intervention (posttest), and 12 weeks after the intervention (follow-up). Variables of interest include, but are not limited to, self-regulation; predictors of snack intake, physical activity, and alcohol use; and interpersonal communication regarding these health behaviors. In addition to surveys, observations will be conducted during the first and fourth lessons, teachers will be interviewed, and focus groups will be held with a selection of students from the intervention condition.

**Results:**

Enrollment started in September 2017. As of June 2019, a total of 1216 participants were enrolled for this trial. Findings will be published in peer-reviewed journals and presented at conferences. The trial has been approved by the Ethics Review Board of the Faculty of Social and Behavioral Sciences of the University of Amsterdam (reference no.: 2017-PC-8244).

**Conclusions:**

In this study protocol, the design of a cluster randomized controlled trial is described, which assesses how effectively the school-based intervention InCharge stimulates healthier lifestyles in late adolescents. We hypothesize that participants in the experimental condition will consume less alcohol, eat fewer unhealthy snacks, and be more physically active compared with participants in the control condition.

**Trial Registration:**

Netherlands Trial Register (NL6654); https://www.trialregister.nl/trial/6654

**International Registered Report Identifier (IRRID):**

RR1-10.2196/17702

## Introduction

### Background

Health and mortality are strongly affected by behaviors such as excessive alcohol use, a poor diet, and physical inactivity [1]. Some health-risk behaviors, such as a poor diet, originate early in life and continue to deteriorate as children grow older [2]. Most health-risk behaviors, however, develop in adolescence. When children move into adolescence, they become less dependent on their parents, peer relationships gain importance, and exposure to high-risk behaviors increases [3]. Generally, unhealthy lifestyle behaviors steadily increase through adolescence, with a peak in late adolescence (age 16 years or older) [4,5]. During this developmental period, several changes in adolescents’ social environment contribute to the accumulation of unhealthy lifestyle behaviors. For example, in late adolescence, most individuals transition from secondary schooling to further education, and the number of adolescents with a part-time job increases with age. Furthermore, older adolescents spend less time in their family home and are increasingly allowed to make their own choices. At the same time, more social activities occur in drinking contexts, and together these changes are associated with unhealthy lifestyle behaviors, such as an escalation of alcohol use [6], a poor diet [7], and decreases in physical activity [8].

### Effectiveness of Health Promotion Programs

In the past decades, numerous health promotion programs have been developed in order to prevent the rapid increase of unhealthy behaviors during adolescence. The majority of these programs take place in the school environment, because many adolescents can easily be reached by school-based health interventions. Several studies have suggested that these interventions can indeed promote healthier lifestyles, such as a healthy diet [9] and physical activity [10], and prevent health-risk behaviors, such as alcohol use [11]. However, most systematic reviews and meta-analyses demonstrated large heterogeneity in effectiveness [10,12].

Furthermore, most health promotion programs include several different components, and in most evaluation studies, the exact relationship between these intervention components and their effects remains unclear. In order to understand which program components contribute to healthier lifestyle behaviors and which components do not, several authors conducted meta-regression analyses. For example, previous research demonstrated that self-regulation, which is defined as the capacity needed to resist temptations and impulses [13], was an effective component in health interventions [14]. Among all prevention strategies that were included in the meta-regression, self-monitoring (ie, observing and recording a target behavior [15]) contributed the most to program effectiveness, and combining self-monitoring with at least one other technique based on self-regulation resulted in the largest effect sizes for both healthy eating and physical activity. Furthermore, research showed that health programs based on improving self-regulation skills were especially effective in late adolescence [12].

Therefore, the school-based health intervention investigated in this protocol study also incorporated self-regulation as the main prevention strategy to promote healthier lifestyles. The intervention, called “InCharge,” is newly developed by the Trimbos Institute (the Netherlands Institute for Mental Health and Addiction). The InCharge program is developed for older adolescents and aims to promote healthier lifestyles by improving self-regulation skills (ie, through elaborating on and practicing self-regulation). The program helps students realize what is important to them and how certain temptations can hinder them from achieving these goals, teaches them that self-regulation can be used to resist certain temptations (eg, peer pressure), trains self-regulation skills by formulating an action plan, and helps them practice self-regulation through various assignments. Finally, alcohol is introduced as a temptation, and students formulate action plans for responsible alcohol use in order to stimulate healthier drinking behaviors.

This protocol study also investigates potential factors that determine the effectiveness of the InCharge school-based health intervention, because previous studies have found large heterogeneity in the effectiveness of these types of interventions [12]. In particular, this protocol study investigates the role of interpersonal communication during the InCharge school-based health intervention. In the context of mass-mediated health interventions, previous studies have shown that interpersonally communicating about health-related topics is strongly related to health behavior [16,17] and that health interventions can indirectly influence health behaviors through stimulating interpersonal communication about a health behavior [18]. This protocol study will investigate similar purposes of interpersonal communication in a school-based health context. Furthermore, as most school-based health interventions are taught by school teachers, this study protocol will also investigate the role of teacher-related communication during the InCharge program.

### Theoretical Basis

The InCharge program is based on several psychological theories such as the social cognitive theory (SCT) [19], the theory of planned behavior (TPB) [20], and the goal-setting theory [21]. The SCT explains behavior by the interaction of personal factors, such as outcome expectancies, self-efficacy, and environmental factors, such as the behavior of others. According to the SCT, behavior change can occur through both active learning and modeling (ie, vicarious reinforcement by learning from the experiences of others). Both mechanisms are incorporated in InCharge; the 7-day challenge offers the opportunity to actively learn through practicing self-control, discussing experiences of classmates with the challenge, and watching several video fragments, resulting in vicarious reinforcement. The TPB is commonly used to explain health behavior and postulates that intention, the most important determinant of behavior, is in turn influenced by the following three constructs: attitude, subjective norms, and perceived behavioral control, which is comparable to self-efficacy in SCT. InCharge mainly aims to influence perceived behavioral control by elaborating on and practicing self-regulation skills. As research has shown that outcome expectancies are related to attitudes [22], the program is expected to influence attitudes by linking the consequences of giving in to health-related temptations to personal goals. Subjective norms are influenced through discussions about social acceptability (regarding alcohol use). Finally, the goal-setting theory explains behavior change by means of an action sequence of wishing, planning, acting, and evaluating [23]. Goals should be both challenging and feasible [24], and plans should connect a certain goal-directed activity with an anticipated situation [25] in order to be successful. These principles are incorporated in the 7-day challenge, which is one of the components of InCharge.

The InCharge program is developed by taking into account the developmental characteristics of older adolescents. The primary developmental tasks of late adolescence are forming an identity, planning the future, and acquiring the necessary skills to transition into adulthood [26]. As older adolescents experience fundamental changes in their self-definition and identity by exploring new philosophies, lifestyles, and behaviors [6], late adolescence is ideally suited to introduce a healthy lifestyle. Previous research on substance use prevention demonstrated that older adolescents benefit from a social influence approach [12], which makes them aware of the various social pressures to use substances in order to be psychologically prepared to resist these influences. The InCharge program also creates awareness of peer pressure by showing and discussing different examples of peer pressure. In late adolescence, the brain considerably matures, improving executive functions, such as planning, thinking ahead, response inhibition, and more advanced self-regulation and impulse control [27,28]. As a result, older adolescents are capable of mastering self-regulation skills, which has been proven to be an effective prevention strategy in this developmental period [12]. Therefore, improving students’ self-regulation skills is one of the core prevention strategies of InCharge.

### Aim and Hypotheses

This study describes the protocol of a randomized controlled trial (RCT) including 70 classes with older adolescents, which aims to evaluate the effectiveness of the InCharge program. Baseline, posttest, and 3-month follow-up measures will be conducted to determine whether the program successfully influences the determinants of health behaviors. After completing the program, students in the intervention condition are expected to refrain more from binge drinking and eating unhealthy foods, such as snacks and sweets, and to be more physically active than students in the control condition.

Other aims of our study are to understand the mechanisms through which the InCharge program has its effects. We investigate whether the effects of the program on health behaviors can be explained by increased self-regulation, which is expected to be one of the core mechanisms of the program. Additionally, as previous research has shown the importance of interpersonal communication in mass-mediated health interventions [18], our study aims to investigate interpersonal communication in the context of a school-based health intervention.

## Methods

### Study Design

The InCharge effectiveness study is a cluster RCT including the following two conditions: an experimental condition (the InCharge program) and a control condition (no intervention) (Figure 1). Participants are older adolescents (aged 16 years or older) in schools for intermediate vocational education, schools for higher general secondary education, and schools for preuniversity education. After initial recruitment and enrollment of schools in the trial, randomization takes place at the class level. In each school, measurements in both experimental and control classes are scheduled 1 week before the four lessons of the InCharge program are implemented in the experimental classes (baseline), and 1 week (posttest) and 3 months (follow-up) after the experimental classes have completed the InCharge program. In addition, the first and fourth lessons of the program are observed by two independent coders in order to obtain information on how the program is delivered, interviews are conducted with teachers about their experiences with the program, and focus groups are conducted with small groups of students about their experiences with the program (both interviews and focus groups are conducted 1 week after the posttest assessment). After all data have been collected within a school, control classes will also receive the intervention.

**Figure 1 figure1:**
[figure not shown]
Design of the cluster randomized controlled trial.

### Participants

#### Recruitment

The Municipal Health Services and prevention departments of regional institutions for the treatment and care of addiction help to implement the InCharge program in schools. From these Municipal Health Services and regional institutions, 47 prevention practitioners are trained by the Trimbos Institute to instruct teachers on how to deliver the program and are asked to provide us with a list of schools in their region interested in participating in the InCharge study. The research team contacts these schools to explain the objective and design of the study. First, schools receive an invitation and an information brochure via email, and thereafter, schools are contacted by phone to discuss participation in the study. Schools are allowed to select the number of classes participating in the study, with a minimum of two classes because randomization occurs within schools. To create comparable research conditions, schools are instructed that a minimum number of two classes should be from the same educational level of the field of study. Classes are eligible for inclusion in the study if they contain older adolescents and the level of education is intermediate vocational education, higher general secondary education, or preuniversity education. Students are recruited by class participation. In collaboration with the schools, students’ parents are informed about the study objectives and receive passive informed consent forms. Written active informed consent is obtained from all participating students.

#### Randomization

We randomize the participants at the class level, and classes within schools are matched on the school level in order to obtain more comparable research conditions. Classes are randomly allocated to the experimental or control condition by means of repeated coin tossing. For each selection of matched classes within schools, classes are assigned to the experimental condition if the coin toss shows heads and to the control condition if the coin toss shows tails. The coin toss procedure is continued until all matched classes are assigned to a research condition, such that as many matched classes as possible are assigned to the experimental and control conditions. Randomization is carried out centrally, with two researchers present to monitor the procedure.

### Sample Size Calculation

Effect sizes are difficult to estimate for the InCharge program because the program is newly developed. As school-based prevention programs generally have small effects [12], we based the estimation of the sample size on a small effect size (*d*=0.2) [29]. In order to reliably detect a small-sized effect in a two-sided test with a conventional significance threshold of *α*=.05 and a power of (1–*β*)=0.80, 393 students are required per condition. However, as students are nested in classes and the program is delivered to classes of students, observations of students in the same class are not independent. Therefore, the required sample size is corrected for clustering. Assuming an intraclass correlation of 0.025 and an average class size of 16 participating students, the required sample size increases to 560 students in 35 classes per condition. Calculations are made using the downloadable procedure “clustersampsi” from Stata (StataCorp).

### Study Intervention

The experimental intervention is a school-based program named InCharge, which has been designed for older adolescents. The main objective of the program is to stimulate healthy lifestyle behaviors, such as increased physical activity, and to decrease unhealthy behaviors, such as binge drinking and eating unhealthy foods. These objectives should mainly be obtained by means of increasing students’ self-regulation skills.

### InCharge Program

The InCharge program consists of four 50-minute lessons, and each lesson contains three assignments of approximately 15 minutes. Teachers are trained on how to work with the program material by prevention professionals from Municipal Health Services or regional institutions for the treatment and care of addiction. Materials, such as worksheets, videos, and a web-based quiz tool, are available on a digital teacher platform. In addition, a specially designed app for the smartphone (the 7-day challenge) is used to help students complete the program.

In the first assignment of the first lesson, students visualize their goals for the next 5 years by thinking about what they want to achieve in life and why this is important to them. In the second assignment, students discuss the biggest temptations in their lives. For this assignment, the teacher clears a space in the classroom and draws an imaginary line. Students are asked to position themselves alongside this imaginary line according to how tempting they assess certain temptations, such as chocolate or sweets, alcohol, and staying in bed in the morning. After each temptation, the teacher asks the students to explain their position. In the third assignment, students visualize how their goals would be affected by repeatedly giving in to their biggest temptations or repeatedly resisting their biggest temptations.

In the second lesson, the concept of self-regulation is introduced (for students, self-regulation is called willpower). First, students watch and discuss a video of the marshmallow experiment to understand the role of self-regulation [30]. In this experiment, young children are offered a choice between one marshmallow provided immediately or two marshmallows after waiting for a short period of time. The second assignment focuses on previous experiences with willpower. Students are asked to discuss their own experiences with succeeded challenges, together with the applied strategies that helped them succeed. Finally, all students prepare a challenge to complete during the next week to train their self-regulation abilities. First, they set a realistic goal for themselves related to a chosen health behavior, after which they create a specific plan to achieve this goal. This plan includes the identification of difficult situations and the selection of coping strategies to address these situations accordingly. The actual challenge is completed as a homework assignment. With the help of a specially designed smartphone app (the 7-day challenge), students monitor their progress.

In the third lesson, first, the results of the 7-day challenge are discussed. During the second assignment, students reflect on their original plan to complete the challenge and discuss how these plans could further be improved. The third assignment addresses peer pressure, as peers have been shown to strongly influence the health behaviors of adolescents [31,32]. In order to grasp the influence of peer pressure, students watch and discuss a video of an experiment with a test subject sitting in a room with confederates. As the room fills up with smoke, all confederates remain calm as if nothing happens. As a result, the test subject also remains seated, which could actually be life threatening in case of a real fire.

The final lesson elaborates on alcohol use. At first, students watch a video of partying adolescents who are consuming large amounts of alcohol. The video shows a group of friends who are having fun at first, but the situation ends with a conflict and an injury as a result of excessive alcohol use. Thereafter, students discuss the role of peer pressure in excessive drinking. Second, in order to make them aware of current social norms, students discuss the social acceptability of binge drinking by means of an interactive web-based quiz. Finally, the students identify situations in their own life, where it is important to be careful with alcohol, and come up with strategies to do so. A more thorough description of the assignments can be found in Multimedia Appendix 1.

### Data Collection

An overview of all measurements is provided in Table 1. Data are collected by means of paper questionnaires, which are answered during school hours under the supervision of a teacher. In addition, observational data are collected during the first and fourth lessons, complemented with qualitative data from individual interviews with teachers and focus groups with a selection of students.

**Table 1 table1:** Overview of measurements.

Measurement		Baseline	Posttest	Follow-up
Demographic variables		X^a^	X	X
**Self-control variables**				
	Perceived self-control/impulsivity	X	X	X
	Perceived temptations	X	X	X
	Motivation to resist temptations	X	X	X
**Alcohol, snacking, and physical activity**				
	Actual behavior	X	X	X
	Intentions	X	X	X
	Attitudes	X	X	X
	Social norms	X	X	X
	Negative outcome expectancies	X	X	X
	Self-efficacy	X	X	X
	Perceived parental rules	X	—^b^	—
**Communication about the program**				
	Frequency (with friends, classmates, and parents)	—	X	—
	Valence (with friends, classmates, and parents)	—	X	—
**Communication about alcohol, snacking, and physical activity**				
	Frequency (with friends, classmates, and parents)	X	X	X
	Valence (with friends, classmates, and parents)	X	X	X
**Program evaluation**				
	Teacher evaluation (student questionnaire)	—	X	—
**Intervention evaluation**				
	Student questionnaire	—	X	—
	Student focus group	—	X	—
	Teacher interview	—	X	—

^a^Measurement performed.

^b^Measurement not performed.

### Outcomes

#### Questionnaire Data

The InCharge program aims to stimulate a healthier lifestyle in general among older adolescents by increasing self-regulation skills. In terms of outcome measures, the study focuses on the following three outcome behaviors: alcohol use, snack intake, and lack of physical activity. A pilot study of the program has shown that these behaviors are most prevalent among older adolescents. The main outcomes that are measured for alcohol use, snack intake, and physical activity are the actual behaviors and predictors of the behaviors. Snack behavior and physical activity are operationalized as the number of times adolescents consume snacks and are physically active in an ordinary week as well as in the past 7 days [33]. Alcohol use is operationalized as the number of times adolescents drink alcohol and engage in binge drinking in the past 4 weeks (ie, frequency), as well as the number of drinks adolescents usually consume on one occasion (ie, quantity). Moreover, the predictors of these behaviors are operationalized according to the TPB as attitudes, subjective norms, perceived behavioral control, and behavioral intention [20]. As an additional predictor, negative outcome expectancies are defined as the anticipated negative result of a certain behavior [34]. We operationalized negative outcome expectancies as the probability that exercising less than once a week or daily snacking will lead to weight increase, a poor condition, and health-related problems. For alcohol use, negative outcome expectancies are operationalized as the probability that drinking more than five glasses of alcohol on one occasion will lead to sickness, loss of control, blackouts, regret, and violence (including sexual violence). Finally, parental rules for the three behaviors are assessed.

Additional measures are general self-control, assessments of various temptations, interpersonal communication about the three health behaviors and the intervention, and evaluation of the program and teacher. First, we assess self-control using an adapted version of the Brief Self-Control Scale [35], which assesses deliberative action and impulse control using the following items: “I am good at resisting temptations,” “I have a hard time breaking bad habits,” “I do certain things that are bad for me, if they are fun,” “I wish I had more self-discipline,” “People would say that I have iron self-discipline,” “Pleasure and fun sometimes keep me from getting work done,” “Sometimes I can’t stop myself from doing something, even if I know it is wrong,” and “I often act without thinking through all the alternatives.” Second, we assess the perceived strength of the temptations with respect to alcohol use, snack intake, and lack of physical activity, as well as the motivation to resist these behavioral temptations. Third, we operationalized interpersonal communication as the frequency of discussions about the intervention (intervention condition only) and the three health behaviors outside class, and how positive or negative adolescents talk about the intervention and these three behaviors. The conversational frequency and valence are separately asked for conversations with friends, classmates, parents, and the teacher who taught InCharge. Fourth, regarding the program evaluation, we assess student perceptions of both the teacher and the prevention program InCharge. The included teacher-related measure is teacher communication, which is operationalized as a selection of variables assessing teacher clarity, verbal immediacy, and content relevance [36-38]. Evaluations of the program consist of an affective (eg, fun) and cognitive component (eg, informative).

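### No measure, wave or analysis set is ranked first among seven behaviour measures, so a false claim of benefit is several times more likely than nominal and the 80% power covers one unspecified test

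*Protocol article*

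**What the plan says.** Under Outcomes, Questionnaire Data, the protocol article gives one status to a large group of variables: "The main outcomes that are measured for alcohol use, snack intake, and physical activity are the actual behaviors and predictors of the behaviors". The same paragraph then defines the measures:

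- Snacking: two recall frames (an ordinary week, the past 7 days).
- Physical activity: the same two recall frames.
- Alcohol: drinking frequency and binge frequency over 4 weeks, and usual quantity per occasion.
- Predictors: four theory-of-planned-behavior constructs plus negative outcome expectancies, for each of the three behaviours.

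The Statistical Analysis section compares the arms on the three behaviours at posttest and at follow-up, and states that this comparison determines the program's effects. It plans both an intention-to-treat and a completers-only analysis. It gives no order among measures, waves or analysis sets, and no rule for declaring the program effective.

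The only significance level in the article is in Sample Size Calculation: "two-sided test with a conventional significance threshold of *α*=.05". The effect size there is generic: "we based the estimation of the sample size on a small effect size", with d=0.2 and no outcome or time point attached. The clustering correction is "Assuming an intraclass correlation of 0.025 and an average class size of 16 participating students", leading to 560 students in 35 classes per condition.

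**The concern.** When many outcomes have equal standing and either wave may carry the claim, one favourable result among many can be reported as showing that the program works. The error rate of that claim is then the chance of at least one false result over the whole group of tests, not 5%. The stated power has the matching weakness: it describes one comparison, while the article's conclusion is a claim on three behaviours.

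This is more than missing detail. The article does address the status of its outcomes, and it makes them all equal. It is also the public text against which later reports will be compared for selective reporting.

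**Working it through.** **1. The plan's own figure.** Inputs from Sample Size Calculation: d=0.2, two-sided 0.05, power 0.80, ICC 0.025, 16 students per class.

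- Unclustered: n = 2(1.960+0.842)²/0.2² = 392.4, so 393 per condition. This matches "a power of (1–*β*)=0.80, 393 students are required per condition".
- Design effect: 1+(16−1)×0.025 = 1.375, and 393×1.375 = 540.4, or 34 classes by the normal approximation.
- With a t distribution on 2(k−1) degrees of freedom for k classes per condition, power is 79.2% at 34 classes and 80.3% at 35. So 35 classes, or 35×16 = 560 students, reproduces. It does so for one test at 0.05.

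**2. Number of tests.** Behaviour measures: 2 (snacks) + 2 (activity) + 3 (alcohol) = 7. Over two waves: 7×2 = 14. If each behaviour were reduced to one score: 3×2 = 6.

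**3. Chance of at least one false result under no effect.** Assumption: each test is two-sided at 0.05, so 0.025 in the favourable direction.

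If independent:
- 14 tests: 1−0.95¹⁴ = 51.2% in either direction; 1−0.975¹⁴ = 29.8% for a false benefit.
- 6 tests: 1−0.95⁶ = 26.5%; 1−0.975⁶ = 14.1%.

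The tests share students, so they are correlated. The article gives no correlations. The values below are assumptions, applied to simulated normal test statistics: 0.5-0.8 within a behaviour, 0.1-0.3 between behaviours, 0.5-0.7 across waves.

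| Tests | Either direction, correlated | Either direction, independent | False benefit, correlated | False benefit, independent |
|---|---|---|---|---|
| 14 | 34-45% | 51% | 17-24% | 30% |
| 6 | 22-25% | 26% | 11-13% | 14% |

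The nominal values are 5% in either direction and 2.5% for a false benefit.

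**4. Power for a three-behaviour family.** Effective size per condition: 560/1.375 = 407.3. Noncentrality: 0.2×√(407.3/2) = 2.854, with 2×(35−1) = 68 degrees of freedom.

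- At 0.05: 80.3%.
- At 0.05/3 = 0.0167, the first step of Holm: 65.5%.
- At 0.05/3 with the baseline value in the model, assuming a correlation of 0.5 with the outcome: noncentrality 2.854/√(1−0.25) = 3.296, power 79.7%.
- Without baseline adjustment, 80% power at 0.05/3 would need 524×1.375 = 720.5, so about 721 per condition, or 46 classes. The 1216 students reported as enrolled would be about 608 per condition if split equally.

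**The case against.** The strongest reply is that an article condenses a fuller plan. A multiplicity procedure, the test level and the scoring of each behaviour are commonly left to an analysis plan, which is not shown. The Statistical Analysis section speaks of three behavioural outcomes, so recall frames or alcohol measures may be combined. Much of this stands. The 0.05 per test is inferred, because the only alpha is in the sample-size paragraph, and seven separate tests per wave is a reading of the measures listed. But no composite is defined, and one score per behaviour still leaves six tests over two unranked waves. An analysis plan that named a single primary would also sit awkwardly with the equal status given in this article.

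The power point depends partly on the remedy. The calculation is correct for one comparison, and the 66% arises only if three primaries are kept.

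Four stronger readings are tempting, and the documents do not support them:

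- That a chance finding of effectiveness is likely. The either-direction figures include chance findings of harm. For a false benefit the range is 17-24% with the assumed correlations.
- That there are 28 tests because of the two analysis sets. Neither set is called main, and they share most students, so doubling the count overstates the problem.
- That the 15 predictors (5 constructs × 3 behaviours) enlarge the effectiveness claim. They are called main outcomes, but the only predictor analysis described under Statistical Analysis concerns treatment integrity within the experimental condition.
- That the hypotheses contradict each other. The abstract expects that students "will consume less alcohol, eat fewer unhealthy snacks, and be more physically active"; the aims expect them to "refrain more from binge drinking and eating unhealthy foods, such as snacks and sweets, and to be more physically active". Binge drinking is one of the listed alcohol measures, so this is a difference in breadth. It does show that the article has not settled which alcohol measure leads.

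**Conclusion.** The point holds. The article gives all behaviours and their predictors equal standing, judges effectiveness at two unranked waves in two unranked analysis sets, and sizes the trial for one test tied to none of them. Followed as written, with each test at 0.05, the chance of at least one false benefit is about 17-24% over 14 correlated tests and 11-14% over 6, against a nominal 2.5%. In either direction it is about 34-45% and 22-26%, against 5%. These ranges rest on the assumed test level and correlations; the upper ends for 6 tests are the independent case. The stated 80% power is right for one test and is about 66% at 0.05/3. The return to about 80% with baseline adjustment rests on an assumed correlation of 0.5.

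**What to change.** Make the choice before outcomes are examined by condition, and record its date. Enrolment and most data collection are already reported, so the timing has to be demonstrable. Either of two routes works:

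1. Name one primary measure, one wave and one analysis set. The 560 per condition and 80% power then stand unchanged.
2. Name one measure per behaviour at one wave in the intention-to-treat set, and test the three with Holm at an overall two-sided 0.05. Adjust for the baseline value, which is already collected, and restate power at the 0.05/3 threshold with the assumed baseline correlation given.

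Under either route, label the remaining measures, the other wave and the predictors as secondary, and the completers-only analysis as a sensitivity analysis. Which measure is primary is the investigators' choice; the article does not decide between the recall frames or the alcohol measures.

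The cost is a few sentences and a dated record. The downside of the second route is a less favourable stated power per outcome, largely recovered if the baseline correlation is near 0.5.
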